**Methods:**

This will be a crossover randomized controlled trial in which 15 individuals will be submitted to three aquatic physiotherapy modalities with a minimum 15-day wash-out period in patients over 50 years old and diagnosed with OA in at least one knee, presence of pain and at least one functional dysfunction for at least 6 months, absence of physical limitation that prevents the exercise protocol from being performed, Kellgren and Lawrence ranking between I and IV, walk independently and without auxiliary device. Variations in the concentrations of MMP-3 and GPx in peripheral blood, pain, edema, and flexibility resulting from the three aquatic physiotherapeutic interventions will be evaluated both pre- and immediate post-intervention. The reference group will be submitted to the same aquatic physiotherapy protocols, however, only the biochemical parameters and the self-perception questionnaires will be evaluated.

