### Outcomes

Initially, all participants will be interviewed and evaluated in relation to the degree of osteoarthritis and functionality. Information regarding the patient data will be confirmed
*via* interview, considering data such as complete name, date of birth, age, affected knee(s), duration of pain, arterial blood pressure, list of medications in use, consumption of tobacco or alcohol, associated diseases, if they are undergoing physiotherapy treatment or regular physical activity.

The classification regarding the degree of osteoarthritis will be performed by analyzing the radiograph of the affected knee according to the method of Kellgren and Lawrence. The radiographs will be analyzed, the degree of osteoarthritis will be identified with the negatoscope support, and the images in the digital form will be displayed on a computer screen, considering the classification expressed in degrees ranging from zero to IV.

Subsequently, the identification of functionality will be assessed according to the Brazilian version of the Knee Injury and Osteoarthritis Outcome Score (KOOS). The KOOS questionnaire was developed in the 1990s as an instrument to evaluate the patient’s perception of their knee and associated problems. Since its first publication in 1998, the psychometric properties of KOOS were evaluated in a systemic review of 37 articles demonstrating adequate validity in its use for the study population.
^
37
^

Regarding the pre- and post-intervention assessment instruments, all participants will have the following parameters evaluated: concentration of MMP-3 and GPx, pain, edema, flexibility, and self-perception of the general well-being. In addition, it should be noted that in the 24-hour-follow-up, only the biochemical concentrations and the self-perception questionnaire will be reevaluated.

The biochemical variables will be measured in peripheral blood from the concentrations of MMP-3 and GPx. The levels of MMPs will be measured based on the Enzyme-Linked Immunosorbent Assay (ELISA) methodology, which is based on the antigen-antibody interaction and will be performed according to the kit manufacturer’s instructions. MMP-3, a constituent of the stromelysin family that is an important mediator responsible for the degradation of collagen type II, IX, and XI,
^
12
^
^,^
^
13

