### Statistical analysis

The resulting data will be tabulated, considering the absolute values and their respective standards. Information regarding the main outcome corresponding to the variations in the concentrations of MMP-3 and GPx in peripheral blood due to three different aquatic physiotherapy interventions will be comparatively evaluated among the distinct interventions and among the different times (in pre- and post-intervention moments).

The information on the outcome regarding pain, edema, and flexibility will be comparatively assessed among the different types of intervention. Statistical analyses will be performed in the SPSS software and will be considered as a significance level when p>0.05 through the repeated measures ANOVA statistical test.

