### Monitoring

*Data monitoring*

We perceive the establishment of a Data Monitoring Committee as unnecessary due to the brief duration of this study and the established safety levels associated with aquatic physiotherapy for patients diagnosed with knee osteoarthritis.

*Harms*

In our study, an adverse event will be defined as any unfavorable functional occurrence in an individual consistently linked to exercise intensity. Adverse events will be documented after the subject provides consent and enrollment in the study. Researchers will evaluate the connection between an event and the exercise intensity of the study protocol, based on a temporal relationship, in addition to assessing whether the event is unexpected or unexplained. The study will meticulously track the subsequent protocol-associated adverse effects: heightened pain, inflammation, and diminished flexibility immediately post-intervention and at the 24-hour mark through patient examination. For any circumstance that may necessitate urgent medical support, the emergency medical service of the Aquatic Physiotherapy department will be activated to ensure the requisite and appropriate assistance.

*Auditing*

Regarding this matter, we find it unnecessary due to the nature of our single-center study, which involves a limited sample size and employs a therapeutic approach that has been well-established as safe.

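### For pain, edema and flexibility the analysis section does not say how the pre-session value enters; adjustment for it should be stated (minor)

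*Protocol article*

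**What the plan says.** The Statistical analysis section of the protocol article treats two sets of outcomes in consecutive sentences. The main outcome, MMP-3 and GPx, "will be comparatively evaluated among the distinct interventions and among the different times (in pre- and post-intervention moments". The functional outcomes, pain, edema and flexibility, "will be comparatively assessed among the different types of intervention". That sentence does not mention time. It also does not say whether the compared quantity is the post-session value, the change, or a baseline-adjusted value. Repeated measures ANOVA is the only test named.

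Other sections show that a pre-session value exists and suggest that it is meant to be used:

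- Outcomes: "Regarding the pre- and post-intervention assessment instruments, all participants will have the following parameters evaluated". The list that follows includes pain, edema and flexibility alongside the two biomarkers.
- Outcomes, on the 24-hour follow-up: "only the biochemical concentrations and the self-perception questionnaire will be reevaluated". Pain, edema and flexibility as outcomes therefore have two readings per session, one before and one immediately after.
- Abstract, Methods: variations in "pain, edema, and flexibility resulting from the three aquatic physiotherapeutic interventions will be evaluated both pre- and immediate post-intervention".
- Trial design: each participant has one session of each program, with at least 15 days between sessions.

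**The concern.** Adjacent sentences describe different comparisons, and the second can be carried out in at least three ways: post-session values, changes, or post-session values adjusted for the pre-session value. These can give different estimates and intervals from the same data.

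A crossover removes stable differences between people. It does not remove a participant's own variation from one session day to another. Knee pain and swelling can plausibly differ on days at least 15 days apart, and the same-session pre value is the measurement that captures this. If it is ignored, that variation stays in the program contrast as noise. If it is simply subtracted, its own measurement error is added.

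With 15 participants, and a sample size argued on biomarkers alone, precision on the functional outcomes named in the article's title is worth protecting.

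**Working it through.** **The plan's own figure.** The only power statement (Trial design) concerns the biomarkers: δ = 3.8, df = 16.143, power 0.95. A two-sided 5% noncentral t calculation with those inputs gives 0.946, so the stated power is reproduced. It says nothing about pain, edema or flexibility, for which the article gives no precision figure.

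**Inputs.** From the article: 15 participants, three sessions each, one pre and one immediate post reading per session. Assumed: all 15 complete all three programs, pre and post variances are equal, and r is the pre-post correlation within a session once each participant's own mean level is removed. The documents give no r, so a range is shown.

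**Relation to ordinary correlations.** If readings correlate ρw within a session and ρb between sessions, then r = (ρw − ρb)/(1 − ρb). For example, ρw = 0.8 and ρb = 0.5 give r = 0.3/0.5 = 0.6; ρw = 0.7 and ρb = 0.6 give r = 0.1/0.4 = 0.25.

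**Variance of a program contrast, relative to post-only = 1.**

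- Change score: 2(1 − r). With two times, a program × time interaction is the same comparison.
- Adjusted for the pre value: 1 − r², before the degree of freedom is paid for.
- Degree-of-freedom cost: 45 readings − 15 participants − 2 for period − 2 for program = 26 residual df. The factor is 1 + 1/(26 − 2) = 1.042, about 4%.

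| r | Change score | Adjusted, net of df cost | Variance reduction, adjusted vs post-only |
|---|---|---|---|
| 0 | 2.0 | 1.042 | none (4% loss) |
| 0.2 | 1.6 | 0.96 × 1.042 = 1.00 | none |
| 0.3 | 1.4 | 0.91 × 1.042 = 0.948 | 5% |
| 0.5 | 1.0 | 0.75 × 1.042 = 0.781 | 22% |
| 0.6 | 0.8 | 0.64 × 1.042 = 0.667 | 33% |
| 0.8 | 0.4 | 0.36 × 1.042 = 0.375 | 62% |

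**Simulation check.** For a 15-participant, three-period crossover with participant, period and program effects (2,500 trials per r), the adjusted analysis gave 1.03, 0.96, 0.77 and 0.37 at r = 0, 0.3, 0.5 and 0.8. The change score gave 1.96, 1.48, 0.99 and 0.40. Mean estimates under no program effect were close to zero for all three analyses, including post-only.

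**Reading the table.**

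- The change score beats post-only only when 2(1 − r) < 1, that is r > 0.5.
- Before the df cost, adjusted is never worse than change, since 2(1 − r) − (1 − r²) = (1 − r)² ≥ 0. After it, change is ahead only if (1 + r) × 1.042 > 2, that is r above about 0.92, and then slightly.
- In interval width, r = 0.6 gives √0.667 = 0.82, about 18% narrower than post-only; r = 0.3 gives √0.948 = 0.97, about 3% narrower.

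**The case against.** A reader might infer that these outcomes are to be compared solely among programs and never over time, so that the pre-session value is thrown away. The documents do not say that. The sentence contains no such exclusion, and the abstract points the other way by speaking of pre-to-post variations. Monitoring also tracks "heightened pain, inflammation, and diminished flexibility immediately post-intervention", which presupposes an earlier reference. The quantity compared may well be the change. This objection stands: the fault is an unsettled and uneven description, not a stated decision to ignore the baseline.

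A reader might also infer that precision is necessarily lost, or that a program given on bad days would look worse. Neither follows. The loss depends on post-only values being used and on an r that is not given, and there is no gain to be had at r of 0.2 or less. Adding a time factor, as for the biomarkers, can make precision worse. Because sequence is randomised and everyone receives all three programs, bad days are not tied systematically to a program; they add noise, not bias.

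Finally, the form of analysis for outcomes other than the main one is often left to an analysis plan, and this is a condensed article. That is a fair reason to rate the point low. It does not remove it, because the article does state an analysis here, and that statement does not match its own abstract.

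**Conclusion.** The point holds in a limited form. The Statistical analysis section names times for MMP-3 and GPx, omits them for pain, edema and flexibility, and does not fix the role of a pre-session value that is collected at every session. The abstract suggests a pre-post comparison, so the two places need to be reconciled.

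The stake is precision in outcomes that the article does not call main; the validity of the program contrast is not in doubt. The size rests on assumed r and equal pre and post variances. It runs from a loss of about 4% in variance at r = 0 to a reduction of 62% at r = 0.8. Severity is minor. The change is worth making because the adjusted analysis is close to or better than both alternatives over the whole range examined.

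**What to change.** Align the Statistical analysis section with the abstract, for instance: *Pain, edema and flexibility will each be analysed as the post-session value in a model with participant, period and program, adjusted for the pre-session value of the same session, entered as its deviation from the participant's mean pre-session value. Adjusted differences between programs will be reported with 95% confidence intervals.*

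A covariate that changes from session to session needs one record per participant and session, so a linear model in that layout should be named in place of, or as the form of, the repeated measures ANOVA for these outcomes.

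The cost is this short text and one residual degree of freedom (about 4% in variance if r is zero). No measurement, visit or participant is added. The article gives the study status as not yet recruiting, so the choice can be fixed before any data are seen.

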**Figure 1. f1:**
[figure not shown]
Flow of interventions and assessment parameters.

For this study, 15 participants will be recruited. The sample size calculation indicated a non-centrality parameter (δ) of 3.8, suggesting a moderate effect on biomarker variations. The critical t-value was 2.10, with degrees of freedom (df) of 16.143, resulting in a total sample size of 15 participants and an actual power of 0.95. The effect size calculation was based on means and standard deviations, and for our main dependent variables, these were reported by previous investigations: Germanou
^
33
^ through the antioxidant levels and Nascimento
^
34
^ through the MMP-2 and MMP-9 analysis between the control and intervention group, in this case, it is represented by patients with knee osteoarthritis.

The assessment parameters used in each variable will consist of instruments that allow for the assessment of the variations in the MMP-3 concentration, oxidative stress, pain, edema, and flexibility. In addition, a self-perception questionnaire, developed by the authors, will be applied to assess self-perception. It consists of a Likert scale where the patient must classify their perception of well-being between zero and 10, where zero represents the worst feeling of well-being and 10 represents the best feeling of well-being. The data collection form, informed consent form and patient identification form can be found as
*Extended data.*
^
32
^ The trial has been registered on
ClinicalTrials.gov (
NCT05610696, 18/01/2023).

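### The only written significance rule has its inequality reversed (p>0.05) and contradicts the article's own sample-size calculation

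*Protocol article*

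**What the plan says.** Under Methods, Statistical analysis, the protocol article names one test and one criterion. Results "will be considered as a significance level when p>0.05", and this is to be judged "through the repeated measures ANOVA statistical test". The same section covers the main outcome (changes in MMP-3 and GPx, compared between interventions and between times) and the comparisons of pain, edema and flexibility between interventions. It gives no other criterion for any of them.

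No other section states an alpha level, a sidedness or a p-value threshold in words. The only other figures that carry this information are in the sample-size paragraph under Methods, Trial design, below Figure 1:

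- a "non-centrality parameter (δ) of 3.8";
- "The critical t-value was 2.10, with degrees of freedom (df) of 16.143";
- from these, 15 people in total, with power given as 0.95.

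**The concern.** A test at the 5% level declares significance when p falls below 0.05. The article prints the opposite inequality. It does so in a complete sentence of running text, so a broken table, a redaction or a missing figure does not explain it.

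The sentence is the step that turns an ANOVA result into a conclusion on the main and the other outcomes. A published protocol exists partly to fix that step before data are seen. As printed, a reader has to guess the intended rule and infer its level from a critical t-value in another section. If the trial is analysed at p<0.05, as it surely will be, its report will formally depart from the published criterion.

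**Working it through.** The check asks what decision rule the sample-size paragraph implies, and then what the printed rule would do if taken literally.

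**Inputs (protocol article, Trial design, sample-size paragraph):** δ = 3.8, df = 16.143, critical t = 2.10, stated power = 0.95.

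**Step 1: reproduce the stated power.** For a two-sided t test, power = P(|T′| > c), where T′ is noncentral t with the stated df and δ, and c is the critical value.

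| Rule | c | Power |
|---|---|---|
| Two-sided 0.05, exact c at df 16.143 | 2.118 | 0.946 |
| Stated c | 2.10 | 0.948 |
| One-sided 0.05 | 1.745 | 0.977 |

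The two-sided rows agree with the stated 0.95 to within rounding of δ: for δ from 3.75 to 3.85, the stated c gives 0.943 to 0.953. The one-sided 0.05 row fits neither the stated critical value nor the stated power.

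**Step 2: the alpha implied by the stated critical value.** 2 × P(T > 2.10) at df 16.143 = 2 × 0.0259 = 0.052. This is slightly above 0.05 because 2.10 is slightly below the exact 2.118.

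**Step 3: direction.** The power of 0.95 is reached only by rejecting when |t| exceeds the critical value. Large |t| means small p, so the calculation presupposes significance for p below about 0.05. The Statistical analysis section prints the reverse.

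**Step 4: the printed rule taken literally.**

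- Under a true null, P(p > 0.05) = 1 − 0.05 = 0.95.
- Under the planned effect (δ = 3.8), P(p > 0.05) = 1 − 0.946 = 0.054. With the stated critical value it is 1 − 0.948 = 0.052.

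**Step 5: sensitivity to df.** A paired t test on 15 participants would have 14 df, not 16.143. That mismatch is a separate matter and does not affect this point. At two-sided 0.05 and δ = 3.8, df = 14 gives c = 2.145 and power 0.942; df = 18 gives c = 2.101 and power 0.949. The direction and the approximate level are the same throughout.

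**The case against.** The strongest reply is that this is a one-character slip in a loosely worded sentence. Nothing suggests that the authors mean to treat large p-values as findings, an analyst reading SPSS output would not do so, and the sample-size paragraph shows what was meant. All of that stands, and it limits the practical weight of the point. It does not make the sentence right. A separate analysis plan, which is not shown, may state the rule correctly, but the published text would still contradict it.

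Three stronger readings are tempting, and the article does not support them.

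- *A reader might infer that every conclusion of the trial will be reversed.* That is the literal consequence of the sentence, not a realistic forecast. The 95% figure restates the reversed sign; it does not estimate a risk the trial will run.
- *A reader might infer that only 5% of true effects would be called significant.* The power of 0.95 belongs to one planned effect size in a t-based calculation built on earlier antioxidant and MMP-2/MMP-9 data. Smaller true effects would pass the literal rule more often than 5% of the time. The article gives no power for pain, edema or flexibility, and none for the repeated measures ANOVA itself.
- *A reader might infer that the article gives no indication at all of level or sidedness.* It gives none in words, but the critical t-value implies both.

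It would also overreach to attach a multiplicity rule or confidence-interval reporting to this correction. An article may leave those to the full protocol or analysis plan.

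**Conclusion.** The point holds as an error of wording with an internal contradiction: the significance criterion is wrong as written. The article's own sample-size figures imply the opposite direction, at about two-sided 0.05 (0.052 from the rounded critical value), and they reproduce the stated power at 0.946 to 0.948.

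The literal error rates, 95% under the null and about 5% at δ = 3.8, rest on the sentence being applied exactly as printed. The second figure also rests on the article's stated δ and df. That the sentence is a slip is an inference, though a strong one, from the sample-size paragraph. The practical consequence is probably small. Correction is still needed because this is the sole pre-specified decision rule for the main and the other outcomes.

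**What to change.** In Methods, Statistical analysis, replace the criterion with: *Results will be considered statistically significant when p<0.05 (two-sided where the test has a direction).* The qualifier is there because the omnibus F test in a repeated measures ANOVA has no direction, while any pairwise t comparison does. This wording agrees with the sample-size paragraph.

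The cost is one sentence. The sample size of 15, the stated power and the choice of test are unaffected by this change. The article gives the study status as not yet recruiting. If that is still so, the correction can be made before any data exist, and it will not look like a later change to the significance criterion.

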### Monitoring

*Data monitoring*

We perceive the establishment of a Data Monitoring Committee as unnecessary due to the brief duration of this study and the established safety levels associated with aquatic physiotherapy for patients diagnosed with knee osteoarthritis.

*Harms*

In our study, an adverse event will be defined as any unfavorable functional occurrence in an individual consistently linked to exercise intensity. Adverse events will be documented after the subject provides consent and enrollment in the study. Researchers will evaluate the connection between an event and the exercise intensity of the study protocol, based on a temporal relationship, in addition to assessing whether the event is unexpected or unexplained. The study will meticulously track the subsequent protocol-associated adverse effects: heightened pain, inflammation, and diminished flexibility immediately post-intervention and at the 24-hour mark through patient examination. For any circumstance that may necessitate urgent medical support, the emergency medical service of the Aquatic Physiotherapy department will be activated to ensure the requisite and appropriate assistance.

*Auditing*

Regarding this matter, we find it unnecessary due to the nature of our single-center study, which involves a limited sample size and employs a therapeutic approach that has been well-established as safe.

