## Methods

### Trial design

This is an interventional transversal study, randomized clinical trial, crossover type with three arms: low, medium, and high-intensity aquatic physiotherapy.

This clinical intervention protocol follows the recommendation from the Standard Protocol Items: Recommendations for Interventional Trials (SPIRIT).
^
31
^
^,^
^
32
^ The study sample, defined according to criteria, will be submitted to a single session of each one of the following modalities of aquatic physiotherapy: (a) low-intensity, (b) medium-intensity, and (c) high-intensity. Among each modality, a minimum of a 15-day wash-out period will be respected, in accordance with
Figure 1.

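### The adverse event definition builds in causality and a functional restriction, so events outside three named effects, or not judged linked to intensity, may go unrecorded

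*Protocol article*

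**What the plan says.** Under Monitoring, the Harms paragraph states that "an adverse event will be defined as any unfavorable functional occurrence in an individual consistently linked to exercise intensity". The article contains no wider definition. Recording starts once the participant has consented and been enrolled.

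The paragraph then adds a relatedness step: "Researchers will evaluate the connection between an event and the exercise intensity of the study protocol, based on a temporal relationship". Researchers also consider whether the event is unexpected or unexplained. Certain effects are tracked by name: "heightened pain, inflammation, and diminished flexibility immediately post-intervention and at the 24-hour mark through patient examination". Urgent situations trigger the emergency service, but nothing says that they are entered as adverse events.

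Three other places bear on this:

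- **Trial design:** participants "will be submitted to a single session of each one of the following modalities of aquatic physiotherapy", and between sessions "a minimum of a 15-day wash-out period will be respected".
- **Outcomes:** at the 24-hour follow-up, "only the biochemical concentrations and the self-perception questionnaire will be reevaluated".
- **Interventions:** the reference group goes through the same programs, but only its biochemistry and self-perception are evaluated.

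On oversight, Monitoring says: "We perceive the establishment of a Data Monitoring Committee as unnecessary". It also waives auditing.

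**The concern.** An adverse event definition should decide what is written down. Whether the intervention caused it is a later judgement. Here the causal judgement is part of the entry condition, and so is a restriction to functional occurrences. An event that the researchers do not attribute to intensity, or do not regard as functional, need never appear in the record. Nobody could then revisit the attribution.

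This matters because safety across intensities is one of the article's motives. The Introduction seeks equally safe programs of differing intensity, and the Conclusions stress safe modulation of intensity. A filter that removes events before they are recorded can only lower the count. With no monitoring committee and no audit, the article describes no independent check that would notice.

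**Working it through.** The plan states no figure on this point, so there is nothing to reproduce. The check sets the definition against the rest of the article.

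**1. Definition against the relatedness step.** The definition requires three things: unfavorable, functional, and consistently linked to intensity. The later sentence has researchers assess the link. If only linked events are adverse events, that assessment has no unlinked ones left to classify. If unlinked events are also to be assessed, the definition is too narrow. The two sentences cannot both be followed as written.

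**2. *Consistently* against the design.** The inputs are one session of each of three intensities per person (Trial design) and the sample size: "For this study, 15 participants will be recruited".

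- Sessions per person: 3 × 1 = 3.
- Sessions in all: 15 × 3 = 45, of which 15 are at each intensity. The reference group's size is not stated and it is not counted here.
- Repeat sessions at the same intensity in one person: 1 − 1 = 0.

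Within one person, each intensity also coincides with one period. Timing can tie an event to a session. It cannot separate intensity from period in that person, nor show that the link repeats.

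**3. *Functional* against foreseeable events.** Eligibility excludes people with uncontrolled hypertension, a history of ischemic heart disease, chlorine allergy, and skin disease that rules out immersion. The article therefore foresees cardiovascular and skin problems. Program C works at Borg 15 to 18. A rash, a faint or palpitations is not plainly a functional occurrence. Inflammation is not plainly one either, yet it is on the named list, so the list and the definition do not match.

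**4. What the named list covers.** Pain, inflammation and flexibility loss are tracked whatever the definition says. Pain, edema and flexibility are also measured before and after each session as outcomes. What remains exposed is everything outside those three effects, and anything not judged linked to intensity.

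**5. The 24-hour point.** Harms promises a patient examination for the three effects at 24 hours. Outcomes confines the 24-hour reassessment to biochemistry and self-perception. These passages conflict.

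**6. How much the reading matters (illustration only).** Assume a per-session event probability *p*, independent across sessions; the article gives no rate. Compare two rules among 15 people with three sessions each:

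- any event counts: 15 × [1 − (1 − *p*)³]
- the event must recur in at least two of the three sessions: 15 × [3*p*²(1 − *p*) + *p*³]

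| Assumed *p* | Persons counted, any event | Persons counted, recurrence needed |
|---|---|---|
| 0.05 | 2.14 | 0.11 |
| 0.10 | 4.07 | 0.42 |
| 0.20 | 7.32 | 1.56 |

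The recurrence rule is one strict way to read *consistently*; the article does not state it. The table shows how widely counts could differ between readings. It does not estimate what this trial would lose.

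**The case against.** The strongest defence reads the paragraph as a whole. The phrase about an individual may only say where the event occurs. The link is to be judged by timing, and a single session can meet that test. The three most likely musculoskeletal harms are tracked by name and called adverse effects, so the authors do not seem to apply the definition literally. The Statistical analysis section plans no comparison of adverse event counts, so no stated analysis is biased.

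Much of this stands. A reader might infer that the definition can never be met, or that almost no events would qualify. The documents do not support that: it holds only if *consistently* means repeated at the same intensity in the same person, and the temporal criterion and the named effects both count against it. A reader might also point to the exact one-sided 95% upper limit for no events in 15 sessions, 1 − 0.05^(1/15) = 0.181. That limit follows from having 15 sessions and would be the same under a perfect definition, so it does not measure this defect.

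The defence does not remove the conflict in the first step. It also leaves events that are neither functional nor on the named list without a clear route into the record. Nor is this a matter of condensation in a journal article, because the rule is stated, not omitted.

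**Conclusion.** The point holds as a defect in a stated definition. Causality and a functional restriction sit inside what counts as an adverse event, in conflict with the separate relatedness step. With one session per intensity, a consistent link within a person cannot be replicated. The likely effect is under-recording of events outside pain, inflammation and flexibility loss, and of events not judged linked to intensity. The direction is towards a safer-looking record.

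The size cannot be given, because the article states no adverse event rate. The conclusion assumes that the definition would be followed as written. If staff record every untoward event regardless, little is lost, but the article does not tell them to. The conflict over the 24-hour examination is separate and does not depend on that assumption. This should be corrected, and since the study status is not yet recruiting, it can be done before any event is lost.

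**What to change.** - Define an adverse event as any untoward occurrence from consent and enrollment to the end of follow-up, whatever its type or suspected cause. Starting at the first session instead would shorten the window that the article already sets.
- For each event, record date, program and session, severity and seriousness. Then judge relatedness in a separate field; the temporal criterion already in the Harms paragraph can serve there.
- List all events, and separately those judged related, by program and by group, including the reference group.
- Reconcile the 24-hour examination under Harms with the 24-hour reassessment under Outcomes.

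The cost is one rewritten definition and, if they are not already there, a few fields on the data collection form, which is not shown here. A few unrelated events will also be listed. Randomization and sample size do not change.
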